**Methods:**

A randomized controlled trial will be conducted among approximately 1500 adolescents aged 12 to 17 years in grades 7-11 of public secondary schools in Brazil. The prospective experimental study design includes measurements at baseline and at 6 and 12 months postintervention. The study groups will consist of randomized classes receiving the standardized EAT intervention (90 minutes of mentoring in a classroom setting) and control classes within the same schools (no intervention). The questionnaire measures smoking status, gender, social, and cultural aspects as well as predictors of smoking. Biochemical validation of smoking status is conducted via random carbon monoxide measurements. The primary end point is the difference of the change in smoking prevalence in the intervention group versus the difference in the control group at 12 months of follow-up. The differences in smoking behavior (smoking onset, quitting) between the 2 groups as well as effects on the different genders will be studied as secondary outcomes.

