### The Education Against Tobacco Intervention

#### Overview

The school-based intervention under evaluation consists of a 90-minute module in the classroom setting. It is presented by 2 medical students per classroom to about 25 pupils at a time discussing features of smoking that students can relate to in their everyday life in a gain-framed and interactive manner. The goal is to initiate and guide the student evaluation process of smoking with age-appropriate information that helps them to reframe a positive nonsmoking image by asking for their opinions and views in small group settings. The students form 4 groups (mostly with their friends) and rotate to 4 different stations in the classroom.

#### Station 1

This station, built up near a window or outside, discusses different tobacco products and extraction of substances of tobacco smoke. In the first part, different products (including e-cigarettes, a water pipe, and cigarettes) are displayed and their functionality and harmfulness are discussed in a gain-framed manner.

Second, the students are instructed to conduct an experiment using a hand-vacuumizer, a napkin, a plastic bottle and a cigarette. The napkin is put between cigarette and bottle and burned down to demonstrate the ingredients of the smoke by the discoloration of the napkin. The process is repeated with e-cigarettes that show little discoloration and are regarded as less harmful but still contain cancerogenic substances [20].

#### Station 2

The attractiveness and photoaging consequences of nonsmoking and mechanisms related to the face are discussed. In the first part, pictures of monozygotic non-/smoking twins are displayed that were extracted from the publication of Okada et al [21]. The students are asked which twin is the smoker and what differences they note.

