### Randomization

In accordance with the guidelines of Good Epidemiologic Practice, randomization is externally and centrally performed via computer by a statistician from the University of Gießen, Germany, on the class level within each school (group allocation is 1:1), which is the strongest method according to the recent Cochrane Analysis [19,33]. Different educational levels within 1 school grade are used for stratification.

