### Participants and Sample Size

In accordance with the first evaluation of our program in Germany, a total of 1500 eligible secondary school students will be recruited [7]. Inclusion criteria are the attendance of grades 7-11 at public secondary schools in Brazil with age ranging from 12 to 17 years. Exclusion criteria are defined as inability to fulfill the inclusion criteria (ie, private schools, different grades). The age range for inclusion in the study is higher than in our German study [10] as the median age of smoking onset is higher in Brazil than in Germany [6,11]. As we expect the same loss-to-follow-up effect as in our quasi-experimental trial in Germany (18.6%), a test power of 70% and a 2-sided alpha of .05 are considered appropriate for our primary end point.

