### Outcomes

The primary end point is the difference of the change in smoking prevalence in the intervention group versus the difference in the control group at 12 months of follow-up. The same longitudinal prevalence effects are studied on our females exclusively as a secondary outcome because our photoaging intervention is suspected to be more successful in females [41]. As our sample size is quite small, the secondary outcome criteria is met if 20% fewer females start smoking in the intervention group during the study period of 1 year. The differences in smoking behavior (smoking onset, quitting) between the 2 groups will be studied as additional secondary outcomes with a positive 20% difference in change of behavior set as met outcome criteria. A smoker is defined as a pupil who claims to smoke at least once in the past 30 days within the survey.

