### Analysis

To examine baseline differences we will use chi-square tests (categorical variables) and *t* tests (continuous variables). The effects of predictors (gender, culture, and social characteristics) on smoking behavior after 12 months (t3) will be calculated by robust panel logistic regression analysis. The significance level is 5% for *t* tests (double-sided) and 95% for confidence intervals (double-sided). Statistical analysis (intention-to-treat) will be performed using SPSS Statistics version 23 (IBM Corp) and STATA 14 (StataCorp LLC). In our sample, the group allocation is not on the individual level but on the class level. In order to take into account this clustering statistically we will use robust panel logistic regression (xtlogit procedure with vce [cluster] option). This procedure is also used to calculate the difference from t1 to t3 of the smoking prevalence in the control group versus the difference from t1 to t3 in the intervention group (our primary end point) by the help of STATA 14.

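### The secondary outcomes are declared met on a bare 20% difference, with no test, interval or link to the primary end point, so chance alone could often supply a pre-specified success

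*Protocol article*

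**What the plan says.** The Outcomes section names one primary end point: the change in smoking prevalence to 12 months, compared between arms. It then adds secondary outcomes with their own success rules.

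- **Girls.** The outcome is introduced as the prevalence effect in females, but its rule concerns onset: "the secondary outcome criteria is met if 20% fewer females start smoking in the intervention group during the study period of 1 year". The section cites the small sample when introducing this rule.
- **Onset and quitting.** These "will be studied as additional secondary outcomes with a positive 20% difference in change of behavior set as met outcome criteria".

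The Abstract lists the same items without order or condition: onset, quitting, "as well as effects on the different genders will be studied as secondary outcomes".

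Error rates appear in two places. Participants and Sample Size states: "18.6%), a test power of 70% and a 2-sided alpha of .05 are considered appropriate for our primary end point". The Analysis section states: "The significance level is 5% for *t* tests (double-sided) and 95% for confidence intervals (double-sided". Neither refers to the 20% rules. Outcomes does not say that a rule also needs a significant result, or whether 20% is relative or in percentage points.

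**The concern.** A rule that calls an outcome met when a point estimate passes a threshold has a false-success rate set only by sampling noise. Few events are expected here: smoking is uncommon in this age group, girls are about half the sample, and quitting can be observed only in the few pupils who smoke at baseline. A 20% gap between arms can easily arise by chance.

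There are several such rules, and none depends on the primary result. Girls' onset is also part of overall onset, so one chance fluctuation can count as two successes. At stake is the reported conclusion: a programme that fails on prevalence could still be presented as having met a pre-specified outcome.

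**Working it through.** **Inputs from the protocol.** Sample: "a total of 1500 eligible secondary school students will be recruited", with 18.6% expected loss. Allocation: "on the class level within each school (group allocation is 1:1". Class size: "presented by 2 medical students per classroom to about 25 pupils at a time". Smoking prevalence in public schools: 5.9% (Introduction).

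- Completers: 1500 × (1 − 0.186) = 1221, about 610 per arm.
- Baseline smokers per arm: 610 × 0.059 ≈ 36. Non-smokers: 610 − 36 = 574, of whom 287 are girls.
- Classes: 1500 / 25 = 60, or 30 per arm.

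**Assumed, because the protocol does not give them.** Half girls; one-year onset of 3–6%, with 15% as a high case; quitting of 30–50%. The main runs ignore class clustering.

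**The plan's own figure.** The 70% power cannot be reproduced because no effect size is stated. The effect it implies can be found from a simple two-proportion comparison at follow-up, without clustering:

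z = [|p1 − p2| − 1.96 √(2p̄(1−p̄)/n)] / √([p1(1−p1) + p2(1−p2)]/n), with n = 610.

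- 5.9% against 2.97%: z = (0.0293 − 0.0231)/0.0118 ≈ 0.53, power 70%. The stated power fits roughly a halving of prevalence.
- 5.9% against 4.72% (a 20% relative reduction): z = (0.0118 − 0.0252)/0.0128 ≈ −1.04, power about 15%.

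At this size, a 20% relative difference is well within chance variation.

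**Each rule under no effect, by hand, at 3% onset and 30% quitting.** An onset rule is met when the intervention rate is at most 0.8 times the control rate. The difference p̂(I) − 0.8 p̂(C) has mean 0.2p and variance p(1−p)/n × (1 + 0.64).

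- Girls, n = 287: 0.006 / √(0.0291/287 × 1.64) = 0.006/0.0129 = 0.47, chance about 32%.
- All non-smokers, n = 574: 0.006/0.0091 = 0.66, chance about 26%.
- Quitting, n = 36, rule p̂(I) ≥ 1.2 p̂(C): 0.06 / √(0.21/36 × 2.44) = 0.06/0.119 = 0.50, chance about 31%.

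**Simulation with exact binomial counts, girls nested in the total (200,000 trials per row).**

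| Onset | Quitting | Girls | Onset, all | Quitting | At least one |
|---|---|---|---|---|---|
| 3% | 30% | 0.34 | 0.26 | 0.32 | 0.60 |
| 3% | 50% | 0.33 | 0.26 | 0.23 | 0.54 |
| 6% | 30% | 0.26 | 0.18 | 0.32 | 0.53 |
| 6% | 50% | 0.26 | 0.18 | 0.23 | 0.47 |
| 15% | 30% | 0.14 | 0.06 | 0.32 | 0.43 |
| 15% | 50% | 0.13 | 0.06 | 0.23 | 0.35 |

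Check on the first row: girls and overall onset are both met in 0.187 of trials, so either is met in 0.335 + 0.262 − 0.187 = 0.410. With independent quitting, at least one is met in 1 − (1 − 0.410)(1 − 0.32) = 0.60. When the girls' rule is met by chance, overall onset is met too in 0.187/0.335 = 56% of trials.

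A class-level intraclass correlation of 0.01–0.02 in onset adds one or two points per row. At 15% onset this puts the range at about 35–44%.

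**Other readings of the rule.**

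- Onset and quitting in percentage points, girls still relative: 29–39% for onset of 2–5% and quitting of 20–50%, nearly all from the girls' rule.
- A favourable two-sided 5% result also required: about 6–7%.

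**The case against.** Four objections deserve an answer.

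**The missing multiplicity scheme may be in a fuller document.** That stands. A condensed article commonly leaves testing order, alpha allocation and labels to the full protocol or SAP, so the lack of a hierarchy alone would not be a finding. But this article goes further: it fixes success as a bare 20% difference. A later document adding a test or an exploratory label would change the published rule, not fill a gap in it.

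**The .05 level is not breached.** That also stands. A reader might infer that the stated .05 was meant to cover all success claims. It was not: the sample size section ties it to the primary end point, and the 5% in Analysis is stated for t tests, which that section names only for baseline comparisons. The fault is that the 20% rules carry no error rate at all.

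**The probability rests on assumptions.** A reader might infer that an ineffective programme would more likely than not meet a rule. The documents do not support that without conditions. They give no onset or quitting rate and no scale for the 20%; even the main range starts below one half, and it falls further at 15% onset or on the percentage-point reading.

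**Three separate rules is one reading.** Onset and quitting share a sentence and might be meant to pass jointly. The girls' rule stands apart in any case, and alone it is met by chance in 26–34% of trials at 3–6% onset.

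**Conclusion.** The concern holds as a badly fixed success rule. With 20% read as relative and applied to point estimates, 1,221 completers, half girls, 5.9% baseline smoking, onset of 3–6% and quitting of 30–50%, an ineffective programme meets at least one rule in roughly 47–60% of trials. The rate is driven mainly by the absence of error control within each rule; the number of rules and the lack of ordering add to it. It drops to about 6–7% only if a significant favourable result is also required, which Outcomes does not say.

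The primary analysis is unaffected. What is affected is what the trial may claim if the primary end point is missed. The change should be made, but the defect does not invalidate the design.

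**What to change.** In Outcomes:

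1. State that only the 12-month primary contrast is confirmatory.
2. Delete both 20% criteria.
3. State that effects on smoking in girls, on onset and on quitting are exploratory, reported as estimates with cluster-robust 95% confidence intervals and not described as met or unmet.

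If the sponsor wants a confirmatory secondary claim, one option is to test the three at two-sided .05 in a fixed order, for example as listed in Outcomes, only after a significant primary result and stopping at the first non-significant one. This is a choice, not a requirement. Ordering alone would not be enough if the bare 20% rules stayed.

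The cost is a wording change before the analysis planned for July 2018, with no extra pupils or data. The downside is that a secondary outcome can no longer be declared a success on a point estimate alone.

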### Data Entry

The data entry is performed manually at the Federal University of Ouro Preto in Brazil by the help of the newest version of Excel (Microsoft Corp) spreadsheet.

### Analysis

To examine baseline differences we will use chi-square tests (categorical variables) and *t* tests (continuous variables). The effects of predictors (gender, culture, and social characteristics) on smoking behavior after 12 months (t3) will be calculated by robust panel logistic regression analysis. The significance level is 5% for *t* tests (double-sided) and 95% for confidence intervals (double-sided). Statistical analysis (intention-to-treat) will be performed using SPSS Statistics version 23 (IBM Corp) and STATA 14 (StataCorp LLC). In our sample, the group allocation is not on the individual level but on the class level. In order to take into account this clustering statistically we will use robust panel logistic regression (xtlogit procedure with vce [cluster] option). This procedure is also used to calculate the difference from t1 to t3 of the smoking prevalence in the control group versus the difference from t1 to t3 in the intervention group (our primary end point) by the help of STATA 14.

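### The pupil-level chi-square and t tests for baseline differences ignore class randomisation and do not hold their nominal 5% level; the effect is confined to the baseline p-values

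*Protocol article*

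**What the plan says.** The Analysis section opens with the baseline comparison: "To examine baseline differences we will use chi-square tests (categorical variables", and t tests for continuous variables. The level is given as "The significance level is 5% for *t* tests (double-sided"; no level is stated for the chi-square tests.

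Later in the same section the article notes that "the group allocation is not on the individual level but on the class level", and gives its remedy: "In order to take into account this clustering statistically we will use robust panel logistic regression (xtlogit procedure with vce [cluster] option". That remedy is a regression. It is named for the 12-month predictor analysis and for the primary end point, and no cluster correction is attached to the baseline tests.

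The Randomization section adds that allocation is made "on the class level within each school (group allocation is 1:1" and that "Different educational levels within 1 school grade are used for stratification". The Overview of the intervention gives the class size: "It is presented by 2 medical students per classroom to about 25 pupils at a time". Under Participants and Sample Size, "a total of 1500 eligible secondary school students will be recruited".

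**The concern.** A standard chi-square or t test takes its standard error from the number of pupils. When classes are allocated whole and pupils in a class resemble each other, the difference between arms varies more from one randomisation to another than that standard error allows. Small p-values then appear too often.

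The article sees this problem for its regressions but names tests for the baseline table that leave it unsolved. This is not a detail left to a fuller document: a method is named, and it conflicts with a principle stated in the same section.

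The tests also answer no useful question. Allocation is by external computer randomisation, so if it was carried out soundly, any baseline difference arose by chance. A small p-value then reflects chance or a wrong standard error, and does not show whether an imbalance matters for the outcome. At stake is a baseline table that may flag spurious imbalances and cast doubt on a sound randomisation.

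**Working it through.** **Inputs from the article**
- Pupils per class: m = 25 (Overview of the intervention).
- Total: 1500 pupils (Participants and Sample Size), so 1500/25 = 60 classes, or 30 per arm at 1:1.
- Level: 5%, two-sided. It is stated for t tests; the same level is assumed here for chi-square.
- Allocation: by class within school, stratified by educational level within grade (Randomization).

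**Assumed, because the article does not give them**
- The ICC.
- The share f of between-class variance that the randomisation strata explain.

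**Step 1. The stated level.** The actual level of a pupil-level test under class allocation is approximately

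level = 2 × (1 − Φ(1.96/√DE)), with DE = 1 + (m − 1) × ICC = 1 + 24 × ICC.

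At ICC = 0, DE = 1 and the level is 5.0%. Without help from stratification, the nominal 5% is reproduced only if pupils in a class are no more alike than pupils in different classes.

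**Step 2. Strata explain none of the between-class variance (f = 0).** The within-stratum and overall ICC then coincide.

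| ICC | DE | Actual level | Multiple of 5% |
|---|---|---|---|
| 0.01 | 1.24 | 7.8% | 1.6 |
| 0.02 | 1.48 | 10.7% | 2.1 |
| 0.05 | 2.20 | 18.6% | 3.7 |
| 0.10 | 3.40 | 28.8% | 5.8 |

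A simulation of 60 classes of 25 (20,000 runs) gave 7.9%, 11.0%, 18.6% and 28.6%. Solving the formula backwards, levels of 10% and 20% correspond to ICCs of about 0.017 and 0.056.

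**Step 3. Strata explain a share f.** Stratified allocation balances that share between the arms, so only the rest inflates the difference:

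DE = (1 − ICC) + 25 × ICC × (1 − f).

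For example, ICC 0.05 and f = 0.5 give 0.95 + 0.625 = 1.575, and a level of 11.8%. Simulation with classes randomised in matched pairs gave:

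| ICC | f = 0.5 | f = 0.8 | f = 0.95 |
|---|---|---|---|
| 0.02 | 7.9% | 6.0% | 5.0% |
| 0.05 | 12.2% | 7.3% | 5.4% |
| 0.10 | 18.4% | 10.3% | 5.1% |

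Setting DE = 1 gives 25 × (1 − f) = 1, so f = 0.96 whatever the ICC. Below that share the test is too liberal; above it the test is conservative. Apart from ICC = 0, this is the only case in which the nominal level holds.

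**Step 4. Age.** Age follows grade, so its overall ICC is high; 0.5 is assumed. The formula in Step 3 gives:
- f = 0: DE = 13, level 59%
- f = 0.8: DE = 3.0, level 26%
- f = 0.9: DE = 1.75, level 14%
- f = 0.95: DE = 1.125, level 6.5%
- f = 1: DE = 0.5, level 0.6%

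A separate simulation took 60 classes in grades 7 to 11, allocated in pairs within grade, with an assumed within-grade age SD of 0.8 years. At residual within-grade ICCs of 0, 0.05, 0.10 and 0.20, the t test rejected in about 0%, 1%, 3% and 9% to 10% of trials. Without stratification it rejected in about 66%. The result for age therefore turns on whether grade is balanced.

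**The case against.** **The design restricts the randomisation.** Classes are allocated within school and, on the natural reading of a terse sentence, within strata lying inside a grade. Figures that assume completely random allocation of 30 against 30 classes overstate the inflation for anything that differs mainly between schools or grades. This stands, and the range in the verdict is conditional on it.

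**A fixed multiplier is not supported.** A reader might infer that false positives are two to four times nominal as a matter of fact. The article gives no ICC, and that multiple needs one of about 0.017 to 0.056 with no gain from stratification. Over the assumed range the multiple runs from about 1 to almost 6.

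**Age is not a clear example.** A reader might infer that a t test on age is almost certain to mislead because age clusters by grade. That holds only if grade is left unbalanced. If the strata balance it, the test can be near nominal or conservative.

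**Nothing downstream uses these tests.** A reader might also infer that spurious imbalances will lead to data-driven adjustment of the primary result. No section makes covariate choice or the primary model depend on baseline p-values. The primary end point is already a change from t1 to t3 compared between arms, analysed with cluster-robust errors. This stands. Nor is the absence of a pre-fixed adjustment set a fault here, since an article may leave that to the analysis plan.

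None of this calibrates the named tests. Stratification moves their true level by an unknown amount, upwards of 5% for some variables and below it for others, and a reader of the baseline table cannot tell which applies.

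**Conclusion.** The point holds, and it is minor. The named baseline tests ignore class allocation and the randomisation strata, against the principle stated in the same section, so their p-values cannot be read at 5%.

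The size depends on assumptions. With 25 pupils per class and a within-stratum ICC of 0.02 to 0.05, the false-positive rate is about 11% to 19%. It is lower where the strata explain much of the between-class variance: about 6% to 7% if they explain 80% of it at overall ICCs of 0.02 to 0.05. It can fall below 5% for age if grade is balanced.

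The consequence is limited to misleading p-values in the baseline comparison. The primary estimate and its standard error are not affected.

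**What to change.** Replace the baseline significance tests with a descriptive table by arm, at pupil and class level, without p-values: numbers of classes and pupils, proportions, means and standard deviations.

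If tests are kept, use comparisons that account for both class and the randomisation strata. Class-clustered errors without the strata would leave out the restriction in the allocation.

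This is a change of wording in the Analysis section. It needs no new data and no change to the conduct of the trial, and the preferred option removes an analysis.

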## Results

[name] raised a grant from the German Heart Foundation that provided funding for the Smokerface App and a grant from the German Center for Lung Research that funded the CO measurement device and the Samsung tablets. The Federal University of Ouro Preto will contribute to the project providing logistic support and copies of the questionnaire to be distributed to every participating student.

The recruitment of schools, participating adolescents, and medical students began in August 2016 and was ongoing until the end of January 2017. The planned period of data collection is February 2017 until June 2018. Data analysis will follow in July 2018 and data presentation/publication will follow shortly thereafter.

